#### Primary outcome

2.6.1

The primary outcome is the change in the Total Nasal Symptom Score (TNSS) from baseline to 2 weeks. The TNSS assesses 4 nasal symptoms (nasal congestion, rhinorrhea, nasal itching, and sneezing) on a five-point scale: 0, no symptoms; 1, mild; 2, moderate; 3, severe; and 4, very severe.^[19]^ TNSS will be measured at every visit, and we will analyze the differences in effects between groups.

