### Statistical analysis

2.12

The statistical analysis will be performed using SAS by an independent statistician who is blinded to the randomized allocation of participants.

All analyses will follow the full analysis set based on the principle of intention-to-treat (ITT); the per-protocol (PP) analysis set will be used for the sensitivity analysis. We will apply the last-observation-carried-forward (LOCF) rule for missing data.

The demographic characteristics and data of both groups will be summarized by means and standard deviations for the continuous variables, and frequencies and percentages will be presented for categorical variables. Differences in baseline between groups will be evaluated by using independent t tests or Mann–Whitney *U* tests for continuous variables and the chi-squared test or Fisher exact test for categorical variables.

Two-sample *t* tests or Wilcoxon rank-sum tests will be used to analyze differences in the primary and secondary outcomes before and after treatment in each group. To demonstrate superiority, we will check whether the upper limit of the one-sided 95% confidence interval (CI) of the difference in the primary outcome between the 2 groups is less than the superiority margin (0.28 points).^[24]^

All participants who participated in at least 1 session will undergo an adverse effect evaluation. All adverse effects reported during the clinical trial will be analyzed. To compare groups and the incidence of adverse events related to the two groups, the chi-square test or Fisher's exact test will be used. The level of significance will be set at 0.05 (2-tailed), except in the case of the primary outcome.

No interim analysis will be performed due to the short duration of the trial.

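### Two tests are allowed for the primary outcome but superiority rests on one unnamed CI limit; on a whole-number TNSS the rank-based route does not fit a 0.28-point threshold

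*Protocol article*

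**What the plan says.** All references are to the protocol article.

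- **Outcome.** Section 2.6.1: "The primary outcome is the change in the Total Nasal Symptom Score (TNSS) from baseline to 2 weeks". The Abstract describes the same outcome as a mean change.
- **Scale.** Section 2.6.1 scores four nasal symptoms "on a five-point scale: 0, no symptoms; 1, mild; 2, moderate; 3, severe; and 4, very severe".
- **Tests.** Section 2.12 offers a t test for two samples as one option and, as the alternative, states that "Wilcoxon rank-sum tests will be used to analyze differences in the primary and secondary outcomes". The comparison is worded as pre- versus post-treatment within each arm. No criterion for choosing between the tests is given.
- **Decision rule.** Section 2.12 then takes a one-sided 95% CI for the between-group difference and asks whether its upper end lies below the "superiority margin (0.28 points"). It does not say which kind of interval is meant.
- **Error level.** Section 2.12: "The level of significance will be set at 0.05 (2-tailed), except in the case of the primary outcome". The primary outcome is therefore judged at one-sided 5%, as the one-sided 95% CI implies.
- **Safeguard.** Section 2.12 has the analysis done by an independent statistician who is blinded to allocation.

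**The concern.** A decision rule written as a CI limit against a number of points needs one defined interval. The t test supplies one, for a difference in means. The rank-sum test supplies a p-value. The interval usually paired with it estimates a location shift, which is a different quantity from the mean difference that the Abstract implies. That interval is also built from pairwise differences between patients, and here those are whole numbers. A threshold of 0.28 points then falls between two possible values and cannot act as a margin. If both routes stay open, the same data can satisfy the rule on one and fail it on the other, with nothing in the text to say which verdict counts.

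**Working it through.** **Inputs.** From section 2.9: 20 per arm and 20% drop-out. The plan's own completer figure reproduces: 40 x (1 - 0.20) = 32, or 16 per arm. From section 2.6.1: four items scored 0 to 4, so one total per visit is a whole number from 0 to 16 and its change is a whole number. Carrying a last observation forward keeps it whole. From section 2.12: one-sided 95% limit and threshold 0.28. The article gives no SD, so an SD of change of 2 to 4 is assumed. Difference = device minus sham, so negative values favour the device.

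**Route 1, mean difference.** Upper limit = d + t(0.95, 2n - 2) x s x sqrt(2/n). With n = 20 and SD 3, the standard error is 3 x sqrt(2/20) = 0.949 and the half-width is 1.686 x 0.949 = 1.60. The rule passes when d < 0.28 - 1.60 = -1.32. With no true effect this has probability of about Phi(-1.32/0.949) = Phi(-1.39) = 8.2%, close to the simulated 8.7%. With a threshold of 0 it would be 5%.

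**Route 2, rank-based shift.** The upper limit is the ordered pairwise difference number n^2 + 1 - C, with C = floor(n^2/2 - 1.645 x sqrt(n^2(2n + 1)/12)).
- n = 20: C = floor(200 - 1.645 x 36.97) = 139, so the limit is difference number 262 of 400.
- n = 16: C = floor(128 - 1.645 x 26.53) = 84, so the limit is difference number 173 of 256.

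Every pairwise difference is a whole number, so the limit is too. No non-integer limit appeared in 32 settings of 8,000 simulated trials. On this route any threshold above 0 and up to 1 gives the same rule (limit 0 or lower). Any threshold above -1 and up to 0 also gives one rule (limit -1 or lower).

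**Printed rule (< 0.28), no true effect, 20 per arm:**

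| Assumed SD | Mean-difference CI passes | Rank-based CI passes | Rank limit exactly 0 | Verdicts differ |
|---|---|---|---|---|
| 2 | 11.9% | 18.6% | 17.9% | 7.0% |
| 3 | 8.7% | 12.7% | 11.1% | 4.5% |
| 4 | 8.2% | 10.6% | 8.7% | 3.2% |

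With 16 per arm the pattern is the same. The lowest disagreement was 2.4% (SD 4, scores held within 0 to 16).

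**Two simulated trials, 20 per arm.**
- Mean difference -0.90: t-based limit 0.632, rank-based limit 0. Under < 0.28 the first fails and the second passes.
- Mean difference -2.60: t-based limit -0.778, rank-based limit 0. Under < -0.28 the first passes and the second fails.

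**How much is due to the margin's sign.** With a threshold of 0, no true effect, 16 or 20 per arm and SD 2 to 4:
- mean-difference CI: 4.4% to 5.3%
- rank-sum test p-value: 4.4% to 5.4%
- Hodges-Lehmann limit below 0: 0.8% to 2.1%, which is conservative
- test chosen by a normality check: 4.4% to 5.4%
- always taking the favourable test: 5.3% to 6.3%

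**Does the disagreement survive a different margin?** At a true difference of -2, a threshold of -0.28 gives opposite verdicts in 8.6% to 13.8% of trials. With SD 3 and 20 per arm it is about 13% (12.2% in a repeat run of 10,000 trials), with success in about 55% on the mean-difference route against 45% on the rank route. With a threshold of 0 the routes differ in 15% to 24%.

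**The case against.** The strongest reply is that the article never mentions a rank-based interval. It lists tests in one sentence and states a CI rule in the next. The Abstract speaks of a mean change, and continuous data are to be summarised by means and SDs, so the natural reading is a CI for a mean difference. The sentence naming the tests also refers to comparisons before and after treatment within each group, so it is not clearly the route to the between-group decision. Naming a t test or its rank counterpart is common shorthand, and the full protocol or an SAP may fix the choice. These points have weight: the shift interval is the standard companion of a permitted test, not something the plan prescribes. They do not close the gap. The sentence names the primary outcome, gives both tests equal standing, and is followed by a rule that only one of them can serve without changing what is estimated.

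A reader might go further and infer that the free choice of test drives the false-positive rate far above 5%. The documents do not support that. The t-based interval alone passes in about 8% to 12% of null trials at 20 per arm under the printed rule, because +0.28 is compared with an upper limit; a t-based limit anywhere from 0 to just under 0.28 passes as well. With the 0.28 rule kept, choosing by a normality check gives 7.7% to 13.7% against 7.4% to 11.6% for the t-based CI, an addition of about 0.3 to 2.1 points. Reporting whichever result is favourable is a worst case, and the blinded statistician makes it less likely. Blinding does not, however, fix the analysis in advance.

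**Conclusion.** The point holds as a mismatch between the permitted analyses and the decision rule. One of the two named tests yields no interval for a mean difference, and on whole-number TNSS changes its usual interval cannot use a threshold of 0.28 points as such. The practical size is the disagreement between routes: about 3% to 7% of trials with no true effect under the printed rule, and about 13% at a true difference of -2, SD 3 and a threshold of -0.28. It is not mainly a false-positive problem. With a zero threshold, free choice of test gives only about 5% to 6%.

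These sizes rest on assumed SDs of 2 to 4, rounded normal changes, one TNSS per visit and the standard order-statistic limit. Averaged scores or an interpolated limit could give non-integer values. The pilot label does not remove the point, since section 2.12 sets a formal superiority rule and the Discussion expects the results to support a wider device approval. It should be corrected, but it does not undermine the trial.

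**What to change.** State in section 2.12 that superiority is decided solely on the one-sided 95% CI for the between-group difference in mean TNSS change from baseline to 2 weeks, taken from one pre-specified ANCOVA with baseline TNSS as covariate. State the direction of subtraction, and that this holds whatever a normality check shows. Keep the rank-sum test as a sensitivity analysis with no role in the decision.

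Baseline TNSS is already collected, and the Discussion notes that randomisation is not stratified by severity, so adjustment also deals with chance imbalance on the primary measure in a trial of 40. The cost is protocol or SAP wording, with no extra patients, visits or data.

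This change does not cure the positive sign of the 0.28 margin. With a mean-difference CI and the rule as printed, an upper limit of 0 would still pass, so the margin needs its own correction.

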### Objective

2.1

The aim of this study is to describe the protocol for a randomized controlled trial designed to clinically assess the effects and safety of intranasal phototherapy for AR in comparison with those of a sham device.

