### Sample size

2.9

Since the aim of this study is to determine preliminary feasibility, there will be no sample size calculation. We will conduct a pilot study with 40 participants (20 in the medical device group and 20 in the sham device group) based on the previous pilot study,^[23]^ and we predict that the drop-out rate will be 20%. Thirty-two patients are predicted to complete the study. This sample size is considered to be sufficient to provide power analysis and sample size calculation for subsequent large-scale definitive RCTs.

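### The superiority rule is wrong as written: an upper one-sided 95% limit below a margin printed as positive 0.28, with no order of subtraction, does not test superiority

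*Protocol article*

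**What the plan says.** Section 2.12 (Statistical analysis) gives the decision rule in one sentence. It takes an upper confidence limit and sets this condition for a superiority claim: "one-sided 95% confidence interval (CI) of the difference in the primary outcome between the 2 groups is less than the superiority margin (0.28 points"). The figure 0.28 has no sign, and the sentence does not say which group is subtracted from which.

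The outcome is defined in section 2.6.1: "The primary outcome is the change in the Total Nasal Symptom Score (TNSS) from baseline to 2 weeks". Each of the four symptoms is scored "0, no symptoms; 1, mild; 2, moderate; 3, severe; and 4, very severe", so a higher score is worse and a fall is an improvement.

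The comparator is a sham. Section 2.1 gives the aim as to "clinically assess the effects and safety of intranasal phototherapy for AR in comparison with those of a sham device".

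On the error level, section 2.12 says: "The level of significance will be set at 0.05 (2-tailed), except in the case of the primary outcome". The primary outcome is therefore judged at one-sided 5%, and the article says so openly.

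Section 2.9 plans "40 participants (20 in the medical device group and 20 in the sham device group") with 20% drop-out.

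**The concern.** A superiority rule has to exclude no difference, or exclude a benefit smaller than a stated margin. On a scale where lower is better, with device minus sham, that means an upper limit below 0 or below a negative number. A limit allowed to reach +0.28 leaves no difference, and a small disadvantage, inside the interval of a trial that has passed.

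This sentence is the only place where the article says what would count as superiority. Section 3 (Discussion) expects the results to give preliminary evidence for a wider approval and to be a basis for a health technology assessment. An analyst who follows the sentence literally would attach the word superiority to a test of a different hypothesis.

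**Working it through.** **Inputs from the article.** Margin 0.28, unsigned (2.12). Upper limit of a one-sided 95% CI (2.12). Higher TNSS is worse (2.6.1). 20 per arm (2.9). Expected completers: 40 × (1 - 0.20) = 32, which reproduces the article's own figure and gives 16 per arm if drop-out is equal.

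**Input not in the article.** The SD of TNSS change. I assume 1.5 to 3.5 points. Only the size of the error depends on this; the logic in step 1 does not.

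**Step 1: which hypothesis is tested.** Let D be the true between-group difference in change (2 weeks minus baseline).

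- *Device minus sham, negative = benefit.* An upper limit below +0.28 rejects H0: D ≥ +0.28. The conclusion is that the device is not worse by 0.28 or more, which is non-inferiority.
- *Opposite sign, positive = benefit.* An upper limit below 0.28 rejects H0: benefit ≥ 0.28. The conclusion is that the benefit is smaller than 0.28.

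With the margin as printed, neither reading tests superiority.

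**Step 2: how often the first reading declares superiority when D = 0.** With equal SDs, SE = SD × √(2/n). The rule passes if D̂ + t(0.95, 2n-2) × SÊ < 0.28. Its probability is that of a noncentral t with 2n-2 degrees of freedom and noncentrality (0 - 0.28)/SE falling below -t(0.95, 2n-2). The critical values are 1.697 (n = 16, 30 df) and 1.686 (n = 20, 38 df).

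Example, n = 20 and SD 2.5: SE = 2.5 × √0.1 = 0.791; noncentrality = -0.28/0.791 = -0.354; probability = 9.7%. A simulation of 200,000 trials also gave 9.7%.

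| n per arm | SD (assumed) | SE | P(superiority declared), D = 0 | Observed difference must be below |
|---|---|---|---|---|
| 16 | 1.5 | 0.530 | 13.0% | -0.62 |
| 16 | 2.5 | 0.884 | 9.1% | -1.22 |
| 16 | 3.5 | 1.237 | 7.7% | -1.82 |
| 20 | 1.5 | 0.474 | 14.3% | -0.52 |
| 20 | 2.5 | 0.791 | 9.7% | -1.05 |
| 20 | 3.5 | 1.107 | 8.1% | -1.59 |

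The last column is 0.28 - t × SE, for example 0.28 - 1.686 × 0.791 = -1.05.

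**Step 3: where the rule has its nominal level.** At D = +0.28 the noncentrality is 0 and the probability is exactly 5% for any SD. At n = 20 and SD 2.5, the probability is 7.8% for a device truly 0.10 worse and 6.1% for one truly 0.20 worse.

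**Step 4: the corrected rules.** With the upper limit required to be below 0, the probability at D = 0 is exactly 5% for any SD. With the limit below -0.28, it is 5% at D = -0.28; at D = 0 it is 2.3% for n = 20 and SD 2.5.

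**The case against.** **A minus sign may simply have been lost.** The article calls 0.28 a superiority margin and looks at the upper limit, which suits a scale where lower is better. With -0.28 the rule would be a sound test of superiority by a margin. This is plausible, and the source cited for the margin is not available to settle it. So the text does not show that the sponsor planned a non-inferiority test, and the point should not be put that way. It also makes the second sign convention in step 1 the less natural reading. But the minus sign and the order of subtraction appear nowhere in the article, so the printed threshold still has to be corrected.

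**A reader might infer that a null or slightly adverse result could be called superior.** For observed results at the assumed SDs, it could not. The last column of the table shows that the observed difference must favour the device by about 0.5 to 1.8 points. An observed zero would pass only if the SD were below about 0.47 (n = 16) or 0.53 (n = 20). What stands is the excess of false positives over 5% when the true difference is zero.

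**A reader might also infer that the one-sided 5% level is an error.** It is a declared exception, and a defensible choice in a pilot. Moving to a two-sided 95% CI would halve the one-sided error to 2.5%. That is a separate trade-off, and correcting the sign does not require it.

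**This is a pilot.** Section 2.9 gives feasibility as the aim and makes no sample size calculation, and section 3 says large trials are needed to confirm effects. Section 2.12 also plans two-sample or rank-sum tests of the outcomes, so a comparison with zero may be reported alongside. This lowers the stakes. It does not make the stated rule a test of superiority.

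**Conclusion.** The point holds: the decision threshold is wrong as written. Without a minus sign and a subtraction order, the rule tests either non-inferiority with a margin of 0.28 or a benefit smaller than 0.28. This conclusion needs no assumption beyond the direction of the scale, which the article gives.

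The size does rest on assumptions. On the device-minus-sham reading with no true difference, superiority is declared in 7.7% to 13.0% of trials at 16 per arm and 8.1% to 14.3% at 20 per arm, for SDs from 3.5 down to 1.5, normal data and equal variances. The nominal level is 5%. The excess is modest at the larger SDs.

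**What to change.** Replace the sentence in section 2.12, before unblinding, with wording such as: *Difference = device minus sham in TNSS change (2 weeks minus baseline); negative favours the device. Superiority is concluded only if the upper limit of the one-sided 95% CI is below 0.* If 0.28 is meant as a minimum benefit, write *below -0.28* instead. If non-inferiority is what is meant, name it so and remove the word superiority.

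The cost is one sentence and a somewhat stricter criterion. At n = 20 and SD 2.5, the observed difference must be below -1.33 (0 - 1.686 × 0.791) for the limit of 0, or below -1.61 (-0.28 - 1.686 × 0.791) for the limit of -0.28, instead of -1.05. The chance of success with a true 1-point benefit falls from 47.8% to 34.4% or 22.7% respectively. The one-sided 5% level can stay as it is.

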### Ethics

2.13

The study will be conducted in compliance with the Declaration of Helsinki and the Korean Good Clinical Practice (KGCP) guidelines. This study protocol was approved by the Institutional Review Board of the Woosuk University Korean Medicine Hospital (WSOH IRB M1807–01–02) and registered in the Clinical Research Information Service (CRIS), which is a primary registry of the World Health Organization International Clinical Trials Registry (https://cris.nih.go.kr/cris/en/search/search_result_st01.jsp?seq=16766). Protocol modifications will be provided to the Institutional Review Board and the trial registry for their approval. Prior to participation, participants will be fully informed about the study and voluntarily sign an informed consent form.

The results of the study will be shared with health care professionals, traditional medicine associations, and other relevant organizations through conferences and will be published in peer-reviewed journals.

## Discussion

3

Due to the limitations of conventional therapies, there is a need to develop alternative treatments for AR. Among them, intranasal phototherapy has received growing interest as an alternative choice to relieve the symptoms of AR patients who cannot take conventional medications because of contraindications or who do not respond well to conventional therapy. Therefore, to investigate the effects and safety of intranasal phototherapy for AR, this proposed trial has been rigorously designed as a randomized, double-blind, placebo-controlled, clinical trial to minimize risks of bias.

In this study, participants will be blinded during the intervention processes using a sham device that is the same in appearance as the treatment device. As the devices will be labeled by the device manufacturer who is not involved in this trial, the investigator operating the device will be blinded to reduce performance bias.

This RCT adopts objective measures such as serum IgE and eosinophil count as well as questionnaires such as the RQLQ to further investigate the mechanisms of action of intranasal phototherapy for AR. In addition, we will utilize the last-observation carried forward (LOCF) rule and intention-to-treat (ITT) approach to manage the attrition bias.

There are some limitations related to the small sample size and lack of sample size calculations. Additionally, we did not stratify demographic factors and characteristics of AR, such as severity and duration of AR, in the randomization process. Therefore, based on the findings of this study, subsequent large-scale definitive RCTs will be needed to confirm the effects and safety of intranasal phototherapy for the treatment of AR.

This protocol was approved by the Korea Food and Drug Administration (KFDA) Investigational Medical Device Application (IMDA). We expect that the results of this study will provide preliminary evidence for broadening the approval range of phototherapy for use in “allergic rhinitis.” Additionally, the results of this study will be the basis for the evaluation of the New Health Technology Assessment (new-HTA).

In 2016, the Korean Medicine Clinical Practice Guideline (CPG) was developed to establish evidence for Korean medicine and strengthen health insurance coverage, and AR is one of the target diseases of the CPG. We expect that the results of this study will contribute to the development of treatment interventions in Korean medicine and establish evidence for “intranasal phototherapy,” which is included as a key question in the Allergic Rhinitis Korean Medicine Clinical Practice Guideline.

## Conclusion

4

This pilot RCT is designed as the first step to explore intranasal phototherapy for AR. The results of this study are expected to be the basis for the design and implementation of large-scale RCTs investigating the effects and safety of intranasal phototherapy for AR.
